# Psychological Effects of Aromatherapy on Smokers With Depressive Tendencies During Smoking Cessation Treatment: Protocol for a Pre-Post Single-Arm Clinical Trial

**DOI:** 10.2196/38626

**Published:** 2022-07-07

**Keywords:** smoking cessation, aromatherapy, depression, cardiovascular risk, inhaler, complementary and alternative medicine

## Abstract

**Background:**

Cessation of smoking can markedly reduce the incidence of cardiovascular disease, improve health economics, and benefit society. Aromatherapy has the potential to be a novel option as an adjuvant therapy for smoking cessation that may alleviate depressive symptoms. However, research on the efficacy of aromatherapy as an adjuvant therapy for smoking cessation is scarce.

**Objective:**

The aim of this study was to examine the potential effects of aromatherapy on psychological states in smokers with depressive tendencies and to determine if it is reasonable to proceed to the next step (ie, a phase III trial).

**Methods:**

This is a pre-post single-arm clinical trial. Smokers with depression will be subjected to aromatherapy during smoking cessation treatment for 12 weeks. We will evaluate changes in scores on the Zung Self-Rating Depression Scale and the Profile of Mood States from pretreatment screening to 4 weeks and 12 weeks after the start of aromatherapy. Moreover, we will compare the group treated with aromatherapy with the group that received standard treatment in our previous randomized controlled trial (ie, the control group in that study). Furthermore, we will compare successful smoking cessation rates after 12 weeks. In addition, we will conduct an exploratory analysis of the efficacy of aromatherapy. The target sample size is 100, which is the number of subjects expected to be enrolled in this study during the 2-year study period.

**Results:**

This study was approved by the Kyoto Medical Center Institutional Review Board (IRB approval No. 19-016). Enrollment started on July 1, 2019. As of May 2022, 76 patients have been recruited. In the original plan, recruitment should have been finished on June 30, 2021. However, the number of subjects decreased due to the COVID-19 pandemic, and the study inclusion period was extended by 1 year (ie, until the end of June 2022) with the approval of the IRB on May 17, 2021. Analyses of the results will be completed subsequently.

**Conclusions:**

This study has some limitations. This is not a rigorous validation study because it compares the same subjects who received standard treatment in a previous study. Moreover, the sample size and methods of statistical analysis were not fully set with prior consideration of statistical rigor. To address these limitations, we plan to conduct a phase III trial that will reflect the exploratory findings of this study. This is the first study to evaluate the psychological effects of aromatherapy during a smoking cessation program, and it may help improve the quality of treatment for smoking cessation in the future.

**Trial Registration:**

UMIN Clinical Trials Registry UMIN000043102; https://tinyurl.com/tn3hvt9w

**International Registered Report Identifier (IRRID):**

DERR1-10.2196/38626

## Introduction

### Psychological Effects of Smoking

Smoking is a major risk factor for noncommunicable diseases (NCDs), such as cancer, chronic obstructive pulmonary disease, diabetes, cerebral infarction, and myocardial infarction [1]. There is an urgent need for active guidance on smoking cessation, not only to reduce the risk of developing NCDs, but also from social and health economics perspectives. Nicotine patches and varenicline are widely used as pharmacotherapies for smoking cessation, as they are known to increase the rate of successful smoking cessation by 2 to 5 times [2-4].

Smoking is known to cause or exacerbate negative emotions [5]. Moreover, the risk of developing depression is higher among smokers than among nonsmokers [6,7]. In addition, smokers with mental disorders show changes in behavior, agitation, and depressed mood after starting smoking cessation treatment, and the rate of outpatient psychiatric visits increases due to worsening of these symptoms [8]. In patients with no mental disorders at the start of smoking cessation treatment, major depression was reported to have occurred in 14.1% of the patients within 12 months of starting treatment [9]. It is well known that nicotine withdrawal can cause depressive symptoms [10], and the Standard Procedure Manual for Smoking Cessation Treatment (version 8.1) states that smoking cessation, with or without treatment, may be associated with a variety of symptoms and may exacerbate underlying mental disorders [11]. Hence, it can be argued that it is essential to adopt a comprehensive approach considering the close relationship between smoking and psychosocial stress, because smoking cessation can lead to temporal worsening of a depressive state and failure to quit smoking, even in those without a history of mental disorders.

### Aromatherapy

Aromatherapy involves the use of essential oils extracted from flowers, leaves, seeds, pericarps, and resins for the treatment and prevention of diseases, physical and mental health, relaxation, and stress relief [12]. Aromatherapy includes methods such as the inhalation of aromas and massage using essential oils diluted in vegetable oils [13]. Among aromatherapy methods, inhalation of essential oils has the advantage of being simple and noninvasive [14]. Once the olfactory cells receive the aroma components of essential oils, sensory information is transmitted from the olfactory nerve to the hypothalamus, which, in turn, acts on the autonomic nervous system via the brainstem. Furthermore, by influencing emotions via the limbic system [15-17], aromatherapy has been shown to alleviate anxiety and depression [18]. This has also been shown to improve sleep quality [19], alleviate fatigue [20,21] and perceived stress [22], and improve cognitive function [23].

### Existing Research on Aromatherapy for Smoking Cessation

Regarding the efficacy of aromatherapy as an adjuvant therapy for smoking cessation, it has been reported that black pepper reduces the urge to smoke [24], and peppermint has been reported to help alleviate respiratory symptoms, such as sputum and cough associated with smoking cessation [25]. Moreover, it has also been reported that various olfactory stimuli, including essential oils, can reduce the urge to smoke [26]. However, high-quality research on this topic is scarce. Furthermore, although it was not a study on treatment for smoking cessation, a systematic review of the efficacy of aromatherapy on depression concluded that it reduces the propensity for depression [18]. In a study in which aromatherapy was applied as an adjuvant therapy, lavender and rosemary were reported to have an anxiolytic effect after smoking cessation [25]. Another study suggested that lavender has anxiolytic and antidepressant-like effects, which are thought to be mediated by the modulation of the N-methyl-D-aspartate receptor and serotonin transporters [27]. Furthermore, exposure to limonene by inhalation, which is found in citrus essential oil, has been reported to increase dopamine levels in the brain [28], and a mechanism of action has been reported for peppermint, suggesting therapeutic efficacy against depression [29]. Furthermore, aromatherapy has been shown to relieve depression, and inhalation is presented as a particularly effective method [30].

### Use of Inhalers as an Adjuvant Therapy for Smoking Cessation

There are various aromatherapy devices, such as aromatherapy inhalers, which are simple and cost-effective for incorporation into daily life. An aromatherapy inhaler is a portable, plastic, lipstick-like container that houses a cotton wick soaked in essential oils. The inhaler enables users to smell the aromas without getting their hands dirty or spilling the oils. Similar “aromasticks” have been used in British hospitals to control symptoms of nausea, insomnia, and anxiety, and to induce relaxation [31,32]. We assume that if aromatherapy inhalers can alleviate psychological and depressive symptoms and reduce cravings for cigarettes, they can form the basis of a novel adjuvant therapy for smoking cessation.

### Hypothesis and Objective

Depression may temporarily worsen during smoking cessation treatment [11]. This study hypothesizes that aromatherapy may help improve this depressive state during treatment. This study aims to examine the effect of adding aromatherapy to standard smoking cessation treatment in patients with depressive tendencies who visited a smoking cessation clinic and to compare these to a historical control group (ie, standard treatment group).

## Methods

### Study Design

This is a pre-post single-arm clinical trial conducted at the National Hospital Organization Kyoto Medical Center in Japan. Patients in this study who visited the smoking cessation clinic at the medical center to receive smoking cessation treatment were assessed using the Zung Self-Rating Depression Scale (SDS) and were classified into two groups: the healthy group (SDS score ≤38) and the depressed group (SDS score = 39-59). Patients in the depressed group are considered to have depressive tendencies. Patients who provide consent will be included in this study, with a target sample size of 100. Smokers with depression will be subjected to aromatherapy during smoking cessation treatment for 12 weeks. Changes in the SDS score and the Profile of Mood States (POMS) score from pretreatment screening to 4 and 12 weeks after the start of aromatherapy will be evaluated. This study will also compare the aromatherapy group with the standard treatment group from a previous study entitled “A Randomized, Multi-center, Double-Blind, Placebo-Controlled Trial for the Effects of Yokukansan on Depressive or Neurotic Smoking Patients during Smoking Cessation Therapy” (University Hospital Medical Information Network [UMIN] ID: 000027036); this group will act as a control group (ie, historical control group). In both studies, only smokers with SDS scores of 39 to 59 were included in the study, and the study subjects were randomly assigned to either the yokukansan group (ie, yokukansan plus standard treatment) or the control group (ie, standard treatment), with 220 subjects in each group. Changes in SDS and POMS scores from pretreatment screening to 4 and 12 weeks after the start of treatment, as well as the rate of successful smoking cessation, will be evaluated. Furthermore, an exploratory analysis on the efficacy of aromatherapy will also be conducted (eg, analyzing the correlation between essential oil preference and smoker information items at the first visit and the changes in essential oil preferences over time).

### Recruitment

#### Inclusion Criteria

In Japan, smoking cessation treatment is covered by health insurance if it is the patient’s first time undergoing the treatment or if more than 1 year has passed since the last treatment. Accordingly, this study included patients covered by health insurance [11] and who met all of the following criteria based on the diagnosis and tests before starting treatment for smoking cessation:

Smokers with nicotine dependence (Fagerström Test for Nicotine Dependence [FTND] score of 5 points or more) who wish to quit smoking.Patients with depression with SDS scores of 39 to 59, based on the self-report questionnaire for assessing propensity to depression.Patients aged 20 to 79 years at the time of the informed consent procedure.Outpatients.Patients whose informed consent has been obtained in writing.

This study aims to include 100 participants in the analysis.

#### Exclusion Criteria

Patients will be excluded from this study if it is determined that they meet any one of the following exclusion criteria based on their diagnosis or test results prior to the start of the study:

Patients whose condition is inappropriate for aromatherapy, that is, those suffering from shock, severe disease states, poor respiratory status, feeling of nausea, or vomiting, etc.Patients who habitually practice aromatherapy.Patients who are unable to smell the aromas of essential oils due to olfactory dysfunction.Patients with a history of epileptic seizures.Patients who are currently on medication for a psychiatric or psychosomatic condition.Patients with an SDS score of 53 points or higher, which is indicative of underlying depression and need for psychiatric consult, and those prescribed medication for a psychiatric and psychosomatic condition [33].Patients with current symptoms of drug allergy.Patients who are pregnant, are lactating, or intend to become pregnant during the study period.Other patients who are deemed to be unsuitable according to the attending physician (patients with severe dementia, poor compliance, etc).

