#### Enrollment and Interventions

The attending physician will provide a complete written explanation and obtain written consent from patients who meet the inclusion criteria. Subsequently, the attending physician will perform subject registration after confirming that the patients meet all the inclusion criteria and none of the exclusion criteria by performing prespecified medical tests.

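### The SDS entry criteria conflict (39-59 against an exclusion at 53 or higher), and the article does not say which range the historical controls span

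*Protocol article*

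**What the plan says.** In the protocol article, Study Design defines the depressed group by an SDS score of 39 to 59, and Inclusion Criteria repeats the range: "Patients with depression with SDS scores of 39 to 59".

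Exclusion Criteria makes any single listed item enough to exclude. One item reads "Patients with an SDS score of 53 points or higher, which is indicative of underlying depression and need for psychiatric consult" and continues "and those prescribed medication for a psychiatric and psychosomatic condition [33]". The item before it already covers "Patients who are currently on medication for a psychiatric or psychosomatic condition".

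Enrollment and Interventions has the physician register a patient only after "confirming that the patients meet all the inclusion criteria and none of the exclusion criteria".

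On the historical controls, Study Design states: "In both studies, only smokers with SDS scores of 39 to 59 were included in the study". It gives 220 subjects per group in the earlier trial. That trial's exclusion criteria are not reported.

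Statistical Analysis compares changes from baseline to week 12 between the two groups by the interaction in a two-way analysis of variance. It names neither a baseline covariate nor a restriction to a common SDS range. Within each group it plans paired t tests.

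**The concern.** Scores of 53 to 59 satisfy an inclusion criterion and an exclusion criterion at once. A reader cannot tell whether these patients, whom the article itself marks as needing a psychiatric consult, were enrolled.

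The conflict reaches the analysis because SDS is both the selection variable and part of the primary outcome. The shared 39-59 range is also the most specific statement the article makes about how alike the two groups are at entry. If the two studies in fact cut SDS at different upper limits, the groups start at different means. The group that starts higher is expected to fall further by regression to the mean alone. An unadjusted comparison of change would count that as a group effect.

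**Working it through.** **Entry range.** Whole-number scores from 39 to 59: 59 - 39 + 1 = 21. Scores from 53 to 59: 59 - 53 + 1 = 7. Scores that meet inclusion and avoid the exclusion: 21 - 7 = 14, namely 39-52. The stated range of 39-59 is therefore not reproduced when the sections are applied together.

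**Alternative reading.** If the exclusion item means SDS of 53 or higher *and* prescribed psychiatric medication, the range stays at 39-59. But current psychiatric or psychosomatic medication is already an exclusion in its own right, so the item then adds little.

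**Consequence for the comparison: two cases.**

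1. The earlier trial applied the same rule. Both groups span 39-52, and the bias from this source is 0.
2. The earlier trial enrolled up to 59 and this one only up to 52. The size then depends on figures that the article does not give.

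**Illustration of case 2.** These inputs are assumptions: clinic SDS normal with mean μ of 38 to 45 and SD 8, baseline to week-12 correlation r of 0.5 to 0.7, no treatment effect. Group sizes are the planned 100 and the 220 of the earlier trial's control arm; using all 220 is also an assumption.

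- Let m be a group's mean baseline after truncation. Expected change = -(1 - r)(m - μ).
- Artefact in the difference in change = (1 - r)(m for 39-59 minus m for 39-52).
- Variance of change in a group = (1 - r)² × variance of truncated baseline + 8²(1 - r²).
- SE = √(variance in the aromatherapy group/100 + variance in the controls/220).

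Worked case, μ = 45 and r = 0.5: the truncated means are 47.22 (39-59) and 45.39 (39-52), a difference of 1.83. Expected change is -0.5 × 2.22 = -1.11 in the controls and -0.5 × 0.39 = -0.19 (rounded down) in the aromatherapy group. The artefact is 0.5 × 1.83 = 0.92. The SDs of change are 7.41 and 7.19, so SE = √(7.19²/100 + 7.41²/220) = 0.88, and the artefact is about 1.05 SE.

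| μ | r | Share of 39-59 scoring 53-59 | Baseline difference | Artefact | SE | Two-sided rejection at 5% | Of which favouring aromatherapy |
|---|---|---|---|---|---|---|---|
| 38 | 0.5 | 7% | 0.74 | 0.37 | 0.87 | 7% | 0.9% |
| 38 | 0.7 | 7% | 0.74 | 0.22 | 0.70 | 6% | 1.1% |
| 45 | 0.5 | 18% | 1.83 | 0.92 | 0.88 | 18% | 0.1% |
| 45 | 0.7 | 18% | 1.83 | 0.55 | 0.71 | 12% | 0.3% |

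The direction is the same throughout: controls appear to improve more. With wider assumptions (mean 36-48, SD 7-10, correlation 0.5-0.8) the artefact runs from about 0.1 to 1.4 points.

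**Check of the remedy.** In a simulation of the same model, analysis of covariance with baseline SDS gave a bias of about 0 and rejection of 4.4-5.4%. This model is linear in baseline, which suits that adjustment.

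**The case against.** A reader might infer that the match with the historical controls fails and that the between-group comparison is biased. The article does not support that. It would mean treating the 39-59 sentence as wrong for this study, because an exclusion narrows it, while treating it as complete for the earlier trial, whose exclusions are not shown. If 39-59 is only the nominal inclusion range of both trials, the earlier one may have carried the same exclusion. This objection stands, and it makes the bias conditional.

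It can also be said that the joint reading lets every section hold, and that a redundant item is not a contradiction. The item might even reach patients prescribed medication after a consult, and so not be quite empty. This stands in part. But the wording most naturally adds a second excluded group, and an eligibility rule should not need this much interpretation.

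A reader might further take the rejection rates of 6-18% as a risk of a false claim of benefit. They are not: false positives in favour of aromatherapy fall to about 1% or less, from the nominal 2.5%. The risk is an understated or missed benefit.

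Finally, the article calls itself exploratory, lists the control group among its limitations, and tests change within the aromatherapy group by paired t tests. A mismatch in the controls does not affect those tests. That limits the reach of the point to the between-group comparison and the eligibility text.

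**Conclusion.** The contradiction in the eligibility text holds. On the natural reading the entry range is 39-52, and the Study Design sentence is wrong for this study. The alternative reading saves the range only by leaving the item with little to do.

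Whether the comparison with the historical controls is biased cannot be determined from the article. The bias from this source is zero if the earlier trial used the same rule. If its controls ran to 59 and this study stopped at 52, the bias is about 0.2-0.9 SDS points against aromatherapy, up to about one standard error, under the assumed clinic mean of 38-45, SD of 8 and correlation of 0.5-0.7. None of these inputs comes from the article.

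**What to change.** 1. Reconcile Study Design, Inclusion Criteria and Exclusion Criteria into one SDS entry range. Which threshold applies is for the sponsor and the investigator to decide.
2. State whether the rule at 53 or higher applied to the historical controls, and correct the sentence that describes both studies together.
3. Tabulate the patients in each group with a screening SDS of 53-59.
4. Run the between-group comparison over the SDS range common to both groups, with baseline SDS as a covariate.

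The cost is protocol wording, a filter on existing data, and a covariate already collected. If some controls scored 53-59, the control sample shrinks by about 7-18% under the assumptions above: 0.07 × 220 ≈ 15 to 0.18 × 220 ≈ 40 patients. The article reports recruitment still open in May 2022 with analyses to follow, so at that point this could be settled before the groups are compared.

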#### Withdrawal Criteria

A subject will discontinue their participation in the study if any of the following occurs:

If a subject informs us of their withdrawal from the study or requests withdrawal of consent.If the attending physician determines that it is inadvisable for the subject to continue participation in the study due to an adverse event (ie, Grade 3 or higher adverse event according to the Common Terminology Criteria for Adverse Events [CTCAE; version 4.0]) [34].If the attending physician determines that continuation of participation in the study is clinically inappropriate due to the exacerbation of a comorbidity or complication.Death.If the attending physician determines that the subject is ineligible to continue the study.If the subject is unable to visit the medical center where the study is being conducted due to relocation or other reasons.

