#### Time Point: 2, 4, 8, and 12 Weeks

We will check for any adverse event and list its grade according to the CTCAE (version 4.0). Aromatherapy adherence status will be rated as follows:

Good: the aromatherapy inhaler is used nearly every day (approximately 80% of the days)Somewhat poor: the aromatherapy inhaler is not used on some days (approximately 60% of the days)Poor: the aromatherapy inhaler is not used on most days (approximately 30% of the days).

SDS scores, physical examination findings (ie, height, weight, abdominal circumference, blood pressure, and heart rate), smoking status, and exhaled CO levels will also be monitored. Further, in weeks 4 and 12, we will collect the POMS self-assessment sheets completed by the patients. At 12 weeks, we will perform the blood tests and perform a confirmation of smoking cessation. We will determine whether or not patients are taking antihypertensive drugs, dyslipidemia drugs, oral diabetes drugs, insulin, sleep medication, and other drugs, specifically anticancer drugs, drugs for hormonal treatment, and steroids. If a subject does not arrive for a scheduled visit, the reason for their absence will be discussed via a phone call. When the reason is hesitation or the unwillingness of a subject to visit the smoking cessation clinic, they will be requested by medical doctors or nurses to visit the hospital. This strategy is described in the Standard Procedure Manual for Anti-Smoking Treatment, which was originally issued in March 2006 by the Japanese Circulation Society, the Japan Lung Cancer Society, and the Japanese Cancer Association (Figure 1).

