### Primary Outcome, Secondary Outcomes, and Procedures

#### Primary Outcome

The primary outcome is the change in SDS and POMS scores [35,41] (ie, depression assessment following smoking cessation), which will be evaluated for the period from the pretreatment screening to 4 weeks and 12 weeks after the start of aromatherapy.

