### Statistical Analysis

Research on the efficacy of aromatherapy as an adjuvant therapy for smoking cessation is scarce. Further, based on our research, the size of the effects of aromatherapy on psychological tests as measured by the SDS and the POMS in smokers has never been reported. Therefore, this study was designed as a pre-post single-arm clinical trial in which the sample size has been determined by considering the feasibility of registration. We will perform a comparison of the aromatherapy group with the standard treatment group from our previous study, “A Randomized, Multi-center, Double-Blind, Placebo-Controlled Trial for the Effects of Yokukansan on Depressive or Neurotic Smoking Patients during Smoking Cessation Therapy” (UMIN ID: 000027036). Similar to this aromatherapy study, the yokukansan study targeted the population of “depressed smoking patients.” For the yokukansan study, 100 patients were registered in our hospital.

Assuming that the registration number of this aromatherapy study would be comparable to that of the previous yokukansan study, this study planned to register 100 patients. The SDS scores and POMS subscale scores at baseline and at the 12-week time point will be compared using paired-samples *t* tests in the aromatherapy group of this study and in the standard treatment group of our previous study. Statistical significance was set at *P*<.05. Furthermore, concerning changes in data from baseline to the 12-week time point, a two-way analysis of variance will be used analyze the interaction between the standard treatment group and the aromatherapy group. The same will be used to compare changes in SDS and POMS scores before and after smoking cessation between the historical control group and the aromatherapy group of this study.

We will also compare the successful smoking cessation rates for a period of 12 weeks from the start of treatment between the standard treatment group and the aromatherapy group. Successful smoking cessation refers to a report of smoking cessation for the past 7 days and an exhaled CO level below 7 ppm. The successful smoking cessation rate was calculated by dividing the number of subjects who successfully stopped smoking 12 weeks after smoking cessation treatment by the total number of subjects who provided consent and received the treatment, multiplied by 100 to give the percentage. Descriptive statistics on subjects’ background data will be generated. No interim analysis will be performed.

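### The withdrawal rule ends study participation, not only aromatherapy, and nothing provides for later SDS or POMS scores; if withdrawn patients fared worse, the week-12 pre-post change is too favourable.

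*Protocol article*

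**What the plan says.** The Withdrawal Criteria open with "A subject will discontinue their participation in the study if any of the following occurs". Six events follow: the patient's own withdrawal, an adverse event, worsening of another condition, death, a physician's finding of ineligibility, and inability to attend. Two are worded as physician judgements on participation: that "it is inadvisable for the subject to continue participation in the study due to an adverse event" (Grade 3 or higher), or that "continuation of participation in the study is clinically inappropriate due to the exacerbation of a comorbidity or complication". The rule governs taking part in the study. The article has no category for a patient who stops the inhaler but is still assessed.

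Under Primary Outcome, "The primary outcome is the change in SDS and POMS scores" from screening to weeks 4 and 12. Under Statistical Analysis, "SDS scores and POMS subscale scores at baseline and at the 12-week time point will be compared using paired-samples" *t* tests. The visit schedule has SDS at weeks 2, 4, 8 and 12 and POMS at weeks 4 and 12.

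For non-attenders, the visit section says "If a subject does not arrive for a scheduled visit, the reason for their absence will be discussed via a phone call". Patients are asked to return when the reason is hesitation or unwillingness. Only the cessation rate, a secondary outcome, keeps every consented and treated patient in its denominator.

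**The concern.** Ending participation normally ends data collection. Some of the listed reasons may be related to the outcome. The Introduction warns that "smoking cessation can lead to temporal worsening of a depressive state", and a severe deterioration could be handled as an adverse event, as an exacerbation or under physician judgement. If patients who do badly leave before week 12, those who remain look better than the treated group really was.

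An analysis plan can choose how to treat missing values, but it cannot recover scores that were never collected. A mixed model would help only so far as the missing scores can be predicted from the recorded ones, and a patient may be withdrawn for a deterioration that has not yet been scored. The trial is meant to inform whether to go on to phase III, so a shift towards improvement would bear on that decision.

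**Working it through.** **Does the plan, followed as written, lose these scores?**

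1. The rule ends participation in the study (Withdrawal Criteria).
2. No section of the article provides for SDS or POMS after that point.
3. The phone contact concerns missed visits, and the request to return depends on hesitation or unwillingness. It does not reach a patient whom the physician has withdrawn.
4. A paired *t* test needs both scores from each patient, so a patient without a week-12 score contributes nothing to it.

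**How large could the bias be?**

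The target of 100 was set by feasibility. The article gives no SD, effect size or dropout rate, so there is no figure of the plan's own to reproduce.

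Inputs from the article: 76 recruited by May 2022; significance at *P*<.05, sidedness not stated and taken as two-sided.

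Inputs assumed, not in the article: SD of SDS change 8; share withdrawn for outcome-related reasons *w*; withdrawn patients' mean change worse than completers' by *d* = 5 to 8 points.

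Let the true mean change over all treated patients be 0 and the completers' mean be *c*. Then (1 − *w*)·*c* + *w*·(*c* + *d*) = 0, which gives *c* = −*w*·*d*. The bias is therefore *w* × *d*, towards improvement. The completers number *n* = 76 × (1 − *w*), rounded, and SE = 8/√*n*. The chance of *P*<.05 is taken from the non-central *t* distribution with non-centrality *w*·*d*/SE.

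| Withdrawn | *n* | SE | *d* | Bias (points) | Rejection of a true null |
|---|---|---|---|---|---|
| 2 of 76 | 74 | 0.93 | 5 | 2/76 × 5 = 0.13 | 5.2% |
| 5% | 72 | 0.94 | 5 | 0.05 × 5 = 0.25 | 5.8% |
| 10% | 68 | 0.97 | 5 | 0.10 × 5 = 0.5 | 8.0% |
| 10% | 68 | 0.97 | 8 | 0.10 × 8 = 0.8 | 12.8% |
| any | – | – | 0 | 0 | 5.0% |

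Sensitivity to the SD at 10% withdrawn, with SD from 6 down to 10 in each case: for *d* = 5 the rejection rate is 10.4% (SD 6) to 6.9% (SD 10); for *d* = 8 it is 19.2% (SD 6) to 10.0% (SD 10). At *d* = 2 it stays between 5.3% and 5.9%.

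**The case against.** The strongest reply is that the article never says assessments stop at withdrawal, and the full protocol, where follow-up after withdrawal might be described, is not shown. This stands as a limit: the loss of scores is inferred from the end of participation. It does not remove the point, because the stated rule reaches participation itself and nothing in the article qualifies it.

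A reader might infer that the rule removes patients because their mood worsens, and that the result is therefore biased. The article does not support that. Worsening depression is not a named criterion, the adverse-event threshold is Grade 3 or higher, patients on psychiatric medication are excluded at entry, and the expected worsening is described as temporary. A temporary dip need not leave a week-12 score 5 to 8 points worse. The bias is conditional.

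A reader might also infer that the comparison with the historical controls is biased in the same direction. The earlier study's withdrawal rule is not given. A similar rule there could cancel part or all of the effect, so neither its direction nor its size can be stated.

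The magnitude rests on assumed inputs. Ten percent of 76 is about 8 patients withdrawn for outcome-related reasons, and nothing in the article supports or excludes that number. Patients withdrawn late also leave SDS at weeks 2, 4 or 8 and POMS at week 4, and week 4 is part of the primary outcome. That softens the loss, but the paired test named in the plan uses week 12.

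Finally, the authors themselves say that this is not a rigorous validation study and that phase III is to follow. That lowers the stakes but is no reason to forgo scores that are cheap to collect.

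**Conclusion.** The point holds in a conditional form. As written, physician-withdrawn patients leave the study with no provision for later SDS or POMS, and so leave the week-12 pre-post comparison. If they fared worse than completers, the mean change is too favourable; if they did not, there is no such bias.

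On the assumptions above, the bias runs from about 0.25 SDS points (5% withdrawn, 5 points worse) to 0.8 points (10% withdrawn, 8 points worse), with the nominal 5% test rejecting a true null about 6% to 13% of the time. With one or two such withdrawals it can be ignored. The actual number is not known from the article. This is a worthwhile and inexpensive improvement, not evidence that the trial's result will be wrong.

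**What to change.** - **Wording.** Leave the listed events and all clinical decisions as they are. Add to Withdrawal Criteria that, except after withdrawn consent or death, these events do not end outcome collection.
- **Patients still in follow-up.** For those who agree, collect the scheduled SDS, POMS and smoking status at the standard cessation visits or by phone. Both questionnaires are self-completed, and staff already ask for omitted items verbally.
- **Patients already withdrawn.** Retrieve any scores that exist in the clinic record.
- **Analysis and reporting.** Include all treated patients with available scores, using SDS at weeks 2, 4 and 8 and POMS at week 4 as well as week 12. Report how many were withdrawn and why, so that a reader can judge which row of the table applies.

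The cost is a short amendment and a few extra contacts. Reach is limited: inclusion was due to end in June 2022 and follow-up in September 2022, so new collection helps only those still being followed. Retrieval and reporting remain possible after that.
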